## Adverse events in TILT and ASSESS-meso participants

Adverse event data is collected at every visit, for all participants in ASSESS-meso and TILT. Whilst participants in ASSESS-meso will not experience any adverse reactions (AR) since they have not received an intervention, it is nonetheless possible that they may experience AEs or SAEs.

Although ASSESS-meso participants are not considered CTIMP participants, some will nonetheless be contributing ‘control’ data to the TILT trial. For clarity and transparency of reporting, all SAEs occurring in ‘control’ participants will be reported to the sponsor in accordance with the specifications below.

Furthermore, because TILT participants will return to follow up in ASSESS-meso following the end of trial, ongoing adverse events monitoring is required in case of any late adverse reactions that present after the 3 month trial period. Reporting of these adverse events will comply with the reporting procedure outlined below. In addition, trial-specific protocol 6b (TSP06b) will contain information on potential adverse reactions to OK432 and BCG, and advice on appropriate management. This TSP will continue to be available for TILT participants once they have returned to ASSESS-meso following the end of trial.

## Reporting procedures

All adverse events will be recorded in the patient’s medical notes and on eCRFs. Depending on the nature of the event the reporting procedures below should be followed. Any questions concerning adverse event reporting should be directed to the trial coordination centre in the first instance.

*Non-serious AE/AR*

All such toxicities, whether expected or not, should be recorded in the adverse events section of the relevant eCRF and on a separate adverse event log for each participant. Non-serious AE/AR do not need to be reported to the trial coordination centre.

*Expected AE*

Expected AE, as listed in section 12.2, should be recorded on the appropriate eCRF and on a separate adverse event log as above. These events do not need be reported as SAE (even if the criteria for such are met) unless the local Principal Investigator deems this necessary.

*Expected AR*

There are a number of expected AR related to both IMPs, including fever, tachycardia, tachypnoea and chest pain following administration. Non serious AR should be recorded on the appropriate eCRF and on a separate adverse event log as above. Serious AR, even if expected, should be reported to the trial coordinating centre and the sponsor in accordance with the specifications below.

*SAR/SAE*

In the case of SAE or SAR, an SAE form (Initial Safety Report Form, I/QMS/SOP/013a) should be completed and faxed/emailed to the trial coordination centre and to the sponsor within 24 hours. The SAE form asks for nature of event, date of onset, severity, corrective therapies given, outcome and causality (as detailed in sections 12.3 and 12.4).

The Principal Investigator should review all SAE forms, and state expectedness and relatedness to the trial. All forms must be signed by the PI (submission of the form by email from the PIs professional address will act as PI signature). Receipt of the form will be reviewed by a delegated member of North Bristol NHS Trust Research and Innovation Department (R&I) and logged on the R&I database. The report may be reviewed by a meeting of members of R&I and a clinical trial pharmacist may be consulting along with the CI, if deemed necessary.

Additional information should be sent within 48 hours if the reaction has not resolved at the time of reporting. Information not available at the time of reporting (such as test results) must be forwarded once available. If the event is ongoing, additional information should be submitted to R&I by fax using the SAE/SAR/SUSAR Follow Up Report Form for CTIMPs (RI/QMS/SOP/013b), available on the NBT website. There is no mandatory requirement regarding the frequency which follow-up reports should be submitted. As a minimum, a report should be submitted when the event resolves/ends.

Fatal or life threatening SAE/SAR should be reported on the day that the local centre is made aware of the event.

The exception is if the SAE/SAR is an expected event, as described in section 12.2, in which case an SAE form does not need to be completed. Expected SAE/SAR should be recorded on eCRFs and on adverse event forms, but do not need not to be reported unless the local Principal Investigator feels there is an important relationship to OK432/BCG.

*SUSAR*

SUSARs must be reported to R&I immediately using the Initial Report Form for CTIMPs (RI/QMS/SOP/013a). There are several reporting requirements for SUSARs. R&I will coordinate the submission of these reports to:

- The main REC (which granted approval for the trial to proceed)
- The MHRA via the eSUSAR electronic reporting system.

The following expedited reporting procedure will apply:

- Fatal or Life-threatening SUSARs - relevant bodies must be notified **as soon as possible** but no later than **7 calendar days** after the CI first has knowledge of the event. Any further information should be forwarded to these bodies within an additional **8 calendar days**.
- Non-fatal or non-life-threatening SUSARs - relevant bodies must be notified **as soon as possible** but no later than **15 calendar days** after the CI first has knowledge of the event. Any further information should be sought and a full report submitted **as soon as possible.**

If the event is ongoing, additional information should be submitted to R&I using the SAE/SAR/SUSAR Follow Up Report Form for CTIMPs (RI/QMS/SOP/013b), available on the NBT website. There is no mandatory requirement regarding the frequency which follow-up reports should be submitted. As a minimum, a report should be submitted when the event resolves/ends.

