## Expectedness

The population of patients involved in TILT is one in which a high number of adverse events are expected. Many of these will unrelated to IMP administration or trial-related procedures, but rather will be a direct consequence of the patient’s underlying malignancy. These expected AE do not need to be reported to the sponsor, even if they meet the criteria for an SAE.

Expected adverse events in these settings are:

- Death due to underlying malignancy
- Admission related to underlying malignancy
- Prolongation of inpatient hospital stay due to underlying malignancy

In addition to these expected AE, there are a number of AR that are well documented and regarded as normal reactions following intra-pleural OK432 or BCG administration. However, because neither IMP has been used in this context in this country before, and because TILT is a feasibility trial, all AR, including expected AR must be reported on eCRFs and, if they meet the criteria for SAR, should be reported to the sponsor in accordance with the guidance below.

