## Data monitoring committee

The TSC will act as a data monitoring committee. All SAE, SAR and SUSAR will be reviewed by the TSC. If there are significant concerns about the safety of the trial, the TSC will have the capacity to stop the trial early. However, since this is a feasibility study, no interim analysis is planned and the TSC will not have the capacity to close the trial based on exploratory clinical outcomes.

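### Section 12.5 both requires and waives reporting of expected serious adverse reactions, and no route is given for exempted serious events to reach the committee said to review all of them

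*Protocol*

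**What the plan says.** Four parts of the protocol bear on this.

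- **Section 12.2 (Expectedness)** separates two classes. Three malignancy-related events (death, admission, prolonged stay) are exempt: "These expected AE do not need to be reported to the sponsor, even if they meet the criteria for an SAE". Reactions to the agents are treated differently, because neither agent has been used in this context in this country and the trial is a feasibility study: "all AR, including expected AR must be reported on eCRFs and, if they meet the criteria for SAR, should be reported to the sponsor".
- **Section 12.5 (Reporting procedures), paragraph on expected reactions**, repeats the second rule: "Serious AR, even if expected, should be reported to the trial coordinating centre and the sponsor in accordance with the specifications below".
- **Section 12.5, paragraph on SAR/SAE**, asks for a form within 24 hours, and same-day reporting of fatal or life-threatening events. It then adds: "The exception is if the SAE/SAR is an expected event, as described in section 12.2", in which case no form is needed. It continues: "Expected SAE/SAR should be recorded on eCRFs and on adverse event forms, but do not need not to be reported". The one override is a judgement by the site's PI that the event has an important link with OK432 or BCG. The double negative in the quoted sentence is evidently a slip for a waiver, since it follows the statement that no form is needed.
- **Section 16.4 (Data monitoring committee)** gives the TSC the monitoring role and the power to stop the trial for safety: "All SAE, SAR and SUSAR will be reviewed by the TSC".

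For controls, section 12.4 says that all of their serious events are covered, and that those "participants will be reported to the sponsor in accordance with the specifications below".

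**The concern.** A site faced with a serious but foreseeable reaction finds one instruction to report it to the coordinating centre and sponsor and another that no form is needed. Two sites could act differently and both be following the protocol. These are the events that section 12.2 singles out for reporting, and BCG is a live organism.

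The committee's remit covers all serious events, yet the reporting rules hold one group of them back from the sponsor and coordinating centre. The protocol does not say how that group gets from the eCRF to the committee. At stake is whether the committee sees the full list when it judges safety.

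**Working it through.** No arithmetic applies, so the check sets the rules side by side.

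| Event | Section 12.2 | Section 12.5, expected AE and AR paragraphs | Section 12.5, exception | Section 16.4 |
|---|---|---|---|---|
| Serious reaction, expected | Report to sponsor | Report to coordinating centre and sponsor | No form; report only if the PI sees an important link | TSC reviews |
| Serious event attributed to malignancy | Exempt | Exempt unless the PI deems a report necessary | Exempt, same PI test | TSC reviews |
| SUSAR | Not addressed | Not addressed | Not affected; own procedure | TSC reviews |

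**Row 1: can the exception be confined to the malignancy events?** It refers to section 12.2, whose explicit list contains only those three. Three things stand against that reading.

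1. The exception names SAR twice. A malignancy event judged unrelated to the agent is an SAE, not a SAR, so on the narrow reading the word has no function.
2. Section 12.1 defines a SAR as a serious event consistent with the product information or listed as expected in the protocol. A serious reaction outside that description is a SUSAR. On these definitions every SAR is expected, so an exception for expected SARs covers all of them.
3. Section 12.3 classes any event judged at least possibly related as a reaction. A SAR has therefore already been linked to the agent. Asking the PI whether the link is important adds a second, higher and undefined threshold.

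The cross-reference is also circular: the expected-reaction paragraph requires reporting according to the specifications that follow it, and those specifications contain the exception.

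**Examples.** Section 12.5 lists fever and chest pain as expected reactions. An admission for either after instillation is serious by section 12.1. The expected-reaction paragraph requires a report; the exception waives it. The same applies to an admission with a known BCG complication if the site treats it as expected. The description of the BCG arm names disseminated infection after intravesical use, and empyema and late pleural infection in earlier intra-pleural trials. Whether the product information classes each of these as expected cannot be checked from the protocol.

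**Row 2: do exempted events reach the TSC?** Section 12.5 puts them in the notes, on the eCRF and on an adverse event log. Section 9.4 adds that eCRFs specifically record deaths. Section 16.4 says the committee reviews all serious events. No section describes a listing or other transfer from the eCRF to the committee. The route is unstated, not closed.

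**The case against.** The strongest reply is that SAR in the exception is a drafting slip: two explicit rules and a stated rationale point the other way, and a careful reader would follow them. That is probably what was intended, and it supports the fix. It does not remove the contradiction, because a site applies the operative paragraph as written and section 12.1 makes the literal reading coherent.

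Other objections limit the point.

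- A reader might infer that exempted events never reach the committee. The documents do not support this: the PI may report voluntarily, deaths and other events are on the eCRF, and section 16.4 does not confine the committee to events sent on a form.
- A reader might infer that serious-event rates will be biased in favour of the agents. Expedited reporting is not data capture. Sections 12.4 and 12.5 have adverse events recorded for all participants in every arm, so an event not sent to the sponsor is still in the trial data.
- A reader might infer that controls report everything while treated participants use the exemption. Section 12.4 ties control reporting to the same specifications, so the wording is ambiguous but does not set up two rules.
- A reader might infer that one attribution call can withhold a treatment-related death. Section 12.3 counts an event with an equally likely other cause as possibly related, hence as a reaction. It sends doubt to the Trial Manager or Chief Investigator, and unresolved disagreement to the MHRA. That safeguard is real, but it works only if serious reactions are then reported, which is what the exception puts in doubt.

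Exempting malignancy-related events from expedited reporting is a deliberate and stated choice. Abolishing it would be a preference, not a correction.

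**Conclusion.** The point holds in two parts. First, the reporting rule for expected serious reactions is contradictory, and the exception read literally cancels the duty for every SAR short of a SUSAR. This rests on the definitions in section 12.1 and the wording of section 12.5, with no outside assumption. Second, the committee's stated remit is wider than the information the protocol arranges to send it.

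The size is a matter of scope rather than of a number. The first part can touch any of the eight people selected for an agent who accept it; the second covers the three malignancy-attributed event types among all twelve participants. No feasibility criterion or efficacy analysis changes. A forecast of how many deaths would be affected would need a residual survival that the protocol does not give for eligible patients, so none is offered.

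**What to change.** 1. In the exception in section 12.5, delete SAR, correct the double negative, and limit the text to the three malignancy events listed in section 12.2. This restores the rule and rationale already given there.
2. In section 16.4, state that the TSC receives a listing by arm, drawn from the eCRF, of all deaths and serious events, including those exempt from expedited reporting. Section 16.3 already sets meetings at least every six months, so the listing can follow that timetable.
3. In section 12.4, state that the same reporting rule, with the same exemption, applies to control and treated participants.

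The malignancy exemption from expedited reporting can stay. The cost is a protocol wording change and a short listing for twelve participants; no new data are collected.

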## Follow-up after adverse events

Participants experiencing SAEs or AEs will receive the appropriate medical treatment as per standard care. SAE/SAR/SUSAR should be followed up until resolution, including follow-up in ASSESS-meso if the event continues after the end of TILT. After recovery or once the event is considered stable, participants will be followed up in the normal trial or study schedule.

## Outcome grading of adverse events

Adverse events are graded as either: resolved, stabilised, on-going, resolved with sequelae or death.

## Reference Safety Information

The following will be used as the Reference Safety Information (RSI) during the course of this trial:

- Summary of Product Characteristics for OK432(Piciban il)/
- Summary of Product Characteristics for BCG (OncoTice)/

If there are any updates made to the document described above, these will be reviewed by the Chief Investigator and Sponsor and a joint decision made whether the updated document will be submitted to the MHRA for use as the RSI in the trial

## Development Safety Update Report (DSUR)

In addition to the expedited reporting above, a Development Safety Update Report (DSUR) will be submitted once a year throughout the clinical trial or on request of a safety report to the sponsor, Competent Authority (MHRA), host NHS Trusts R+D departments and the REC via the Health Research Authority (HRA).

# STATISTICAL ANALYSIS

## Primary outcome measure

The primary outcome measure is feasibility, which will be assessed based on the following criteria:

- Recruitment rates to TILT
- Feasibility of identifying and randomising 12 eligible participants
- Acceptance rates for intra-pleural OK432/BCG following random selection
- Collection of data on participants who declined to receive OK432/BCG when offered it
- Collection of data on participants within ASSESS-meso who declined to be considered for future trials
- Number of participants in the control arm who were aware of the intervention arm
- Attrition rates and data completeness rates

In addition to feasibility data, qualitative interviews will be undertaken with participants and focus groups with their relatives/carers to explore the acceptability of trial processes. Analysis of the qualitative data is described in Section 10.3.

## Secondary outcome measures

Secondary outcome measures will collect exploratory data on the clinical efficacy of OK432 and BCG. This data will be used to decide the primary outcome for the subsequent full-scale trial, and to estimate the variance of the chosen outcome for a sample-size calculation. Potential outcomes include:

- Tumour response, based on CT appearances at baseline and 12 weeks ^42^
- Overall survival (OS), defined as time between date of diagnosis with MPM to date of death, censored 12 weeks after the final trial visit of the final participant
- Progression-free survival rates (PFSR) at 12 weeks
- Patient-reported chest pain and breathlessness, measured on visual analogue scales (VAS)
- Patient-reported quality of life, measured using the EQ-5D-5L health questionnaire
- Pleurodesis rates, defined as pleural fluid drainage of less than 50ml on 3 consecutive occasions, with <25% opacification on CXR or <250ml pleural fluid on thoracic ultrasound scanning (TUS)
- Time to pleurodesis, calculated from baseline assessment to date of pleurodesis
- Biomarker response assessed using serial serum and pleural mesothelin levels

Participants will be followed up until death, or end of trial (EoT) 12 weeks after the final trial visit of the final participant, whichever is sooner.

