- Qualitative interviews with participants and their relatives to explore the acceptability of trial processes.

Secondary outcome measures will collect exploratory data on the clinical efficacy of OK432 and BCG. They will include:

- Tumour response, based on CT appearances at baseline and 3 months, assessed using modified RECIST^42^
- Overall survival (OS), defined as time between date of diagnosis with MPM to date of death, censored at the end of the trial (EoT)
- Progression-free survival rates (PFSR) at 3 months
- Patient-reported chest pain and breathlessness, measured on visual analogue scales (VAS)
- Patient-reported quality of life, measured using the EQ-5D-5L health questionnaire
- Pleurodesis rates, defined as pleural fluid drainage of less than 50ml on 3 consecutive occasions, with <25% opacification on CXR or <250ml pleural fluid on thoracic ultrasound scanning (TUS)
- Adverse events
- Biomarker response assessed using serial serum mesothelin levels.

Following completion of the trial, participants will return to follow up within ASSESS-meso cohort study until death or withdrawal from the cohort. This will yield additional data over time, and consequently a priori analyses are planned at 1 year and 2 years post-completion of TILT (i.e. following the final visit of the final participant) to evaluate overall survival, progression-free survival, adverse events and other long-term clinical outcomes.

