## TILT and ASSESS-meso related activities

Screening for TILT eligibility and subsequent randomisation of eligible participants are designated ASSESS-meso activities. They are included in the TILT protocol and flow diagram for clarity.

Participants who are selected to participate in TILT will be asked to provide further written informed consent for TILT. If they consent to participate, the first TILT-related activity will be the intervention visit. Participants who decline to join TILT and participants who are not randomly selected will continue to undergo follow up assessments ASSESS-meso. Follow up of these participants will be organised to match the TILT follow up schedule, in accordance with the flexible follow-up schedule stated in the ASSESS-meso protocol.

Participants will only be considered to be participating in the TILT trial if and when they have signed the TILT consent form. All activities that are undertaken prior to TILT consent are considered ASSESS-meso related activities and are included in the ASSESS-meso protocol.

For ease of statistical analysis, TILT follow up assessments will be timed from the point of randomisation, i.e. Week 0 will be the Screening Visit even though this is not an official TILT-related assessment. This is preferable to using TILT consent date as Week 0, as there is no equivalent visit for the ‘control’ participants in ASSESS-meso (as they are not asked to give further consent). No TILT-related activities will take place between randomisation and the participant providing consent for TILT. The time between the two visits is expected to be a few days, to allow the participant sufficient time to consider the TILT Participant Information Sheet, and decide whether they wish to enrol in the trial.

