## End of trial (EoT)

Trial recruitment will cease in November 2019, regardless of the number of participants enrolled. EoT date, therefore, will be 12 weeks after enrolment of the 12^th^ trial patient or 12 weeks after the recruitment window closes, whichever happens first. At EoT, participants will return to clinical follow up within ASSESS-meso, which will continue until death, loss to follow up or withdrawal from the study. Data from ASSESS-meso will be used to evaluate overall survival at EoT.

|  |  | **Screening**  **Week 0*** | **Intervention**  **Day 0-14** | **3 days post-intervention**  **(Week 3)** | **Week 6** | **Week 12** |
| --- | --- | --- | --- | --- | --- | --- |
| **Clinical assessment** | Assessment of eligibility | X | **X** |  |  |  |
|  | History of pleural interventions | X |  | X | X | X |
|  | Previous oncological treatment | X |  |  |  |  |
|  | Medication history | X | **X** | X | X | X |
|  | WHO/ECOG performance status | X | **X** | X |  |  |
|  | Vital signs, pulse oximetry | X | **X** |  |  |  |
|  | Physical examination | X |  |  |  |  |
|  | Insertion of IPC (if not already in situ) | X |  |  |  |  |
|  | Pleural fluid drainage diary review | X |  | X | X | X |
|  | Documentation of AEs |  | **X** |  | X | X |
| **Blood tests** | Screening blood tests (HIV screen, hepatitis screen, immunoglobulins, random glucose, thyroid function tests) | X |  |  |  |  |
|  | Pregnancy test  (if female <55 yrs) | X |  |  |  |  |
|  | Coagulation panel | X |  |  |  |  |
|  | Trial blood tests (Full blood count, urea & electrolytes, liver function tests, C reactive protein) | X | **X** | X | X | X |
|  | Serum mesothelin | X |  | X | X | X |
|  | Pleural fluid sampling and storage | X | **X** | X | X | X |
|  | Mantoux test (if logistically possible, BCG arm only) | X |  |  |  | X |
| **Randomisation & intervention** | Random selection | X |  |  |  |  |
|  | Informed consent for TILT |  | **X** |  |  |  |
|  | Administration of OK432/BCG |  | **X** |  |  |  |
| **PROMS** | Breathlessness & chest pain VAS score | X |  | X | X | X |
|  | Daily VAS score completion |  |  |  |  |  |
|  | EQ-5D-5L QoL questionnaire | X |  | X | X | X |
| **Radiological imaging** | Chest x-ray | X | **X** | X | X | X |
|  | Thoracic ultrasound | X | **X** | X | X | X |
|  | CT chest (within preceding 2 weeks) | X |  |  |  | X |
| **Qualitative research** | Participant interviews |  |  |  |  | X |
|  | Focus groups with relatives/carers |  |  |  |  | X |

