## Analysis plan

Basic descriptors will be used to summarise the characteristics of the overall trial population, each arm, and participants who decline any element of the trial. The characteristics of people who decline participation will be compared with the trial population using means, confidence intervals, chi-squared and unpaired T-tests. If possible, multivariable regression modelling will be undertaken to explore which factors were associated with non-acceptance of OK432/BCG.

Feasibility outcomes, including recruitment, randomisation and trial completion rates, will be described for the overall trial and for each arm. Secondary outcomes will be summarised for each arm based on randomisation, i.e. intention to treat. Per protocol and compliance averaged causal effects (CACE) analysis will be undertaken as secondary analyses for clinical efficacy outcomes.

Time to event data will be analysed using the Kaplan-Meier method. Cox proportional hazards modelling will be used to calculate hazard ratios for death and pleurodesis. Univariable modelling will be used, followed by multi-variable methods to control for potential confounders. The time-independent confounders to be considered are age, sex, performance status, tumour histology and whether chemotherapy was received. Time-dependent confounders that will be adjusted for are the time between diagnosis with MPM and baseline assessment, and length of time the IPC was in situ. The main analysis will include all patients. A priori sub-group analyses will stratify patients according to time since diagnosis (≥8 weeks versus <8 weeks) and whether chemotherapy was received.

Pleurodesis rates will be calculated for the whole population, and in the sub-group of patients who’s IPC had been in situ for less than 6 weeks at baseline assessment.

Outcomes with repeat measurements, e.g. PROMS and biomarker responses, will be analysed using regression modelling with adjustment for baseline values. Survival rates will be compared with national survival data, and survival rates from previous clinical trials of new treatments in MPM. Progression-free survival rates will be compared to validated values for acceptable clinical activity of new oncological agents in MPM.^99^

Statistical analysis will be undertaken using Stata (StataCorp LP) version 14, with support from YTU.

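### Overall survival is timed from diagnosis without delayed entry, which inflates absolute survival and the comparison with national data, and its censoring date is defined in two incompatible ways

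*Protocol*

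**What the plan says.** **Time origin.** Sections 2.3 and 13.2 both start OS at the date of diagnosis; 13.2 reads "Overall survival (OS), defined as time between date of diagnosis with MPM to date of death, censored 12 weeks after the final trial visit", that visit being the last participant's. Section 6.4 identifies eligible patients at assessment visits during ASSESS-meso follow-up and randomises them at Week 0. Section 5.5 uses that date as the trial's clock: "TILT follow up assessments will be timed from the point of randomisation". Time to pleurodesis in section 13.2 runs from baseline.

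**Analysis.** Section 13.3 specifies Kaplan-Meier, then univariable and multivariable Cox models. The interval from diagnosis to baseline is among the adjustment variables and is called time-dependent. Subgroups are split at 8 weeks since diagnosis. The section adds: "Survival rates will be compared with national survival data, and survival rates from previous clinical trials of new treatments in MPM".

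**Cut-off.** Section 2.3 has OS "censored at the end of the trial (EoT"). Section 9.6 gives that date two triggers. One is the twelfth enrolment plus 12 weeks. The other is "12 weeks after the recruitment window closes, whichever happens first". Section 13.2 instead places both OS censoring and EoT 12 weeks after the last participant's final visit, which section 9.1 schedules at Week 12.

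**The concern.** Nobody can enter the analysis without having lived from diagnosis to randomisation. When that interval counts as time at risk, no death can occur in it, and the Kaplan-Meier curve stays too high. National data that follow everyone from diagnosis include the early deaths that TILT cannot observe, so the comparison favours TILT whatever the agents do.

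The diagnosis-to-baseline covariate does not cure this. It enters the multivariable Cox model only and leaves the Kaplan-Meier estimates, the univariable model and the external comparison as they were. It is also fixed at baseline, so the time-dependent label is wrong.

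Section 13.2 uses the secondary outcomes to choose the next trial's primary outcome and to estimate its variance. An inflated OS, whose spread includes variation in the lag, would carry into that design. The two cut-off dates would also give two different OS data sets, with nothing in the protocol to say which applies.

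**Working it through.** The protocol gives no survival calculation to reproduce; section 6.6 bases the 12 participants on earlier feasibility studies.

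**Inputs from the protocol.** Average survival of 9 to 14 months from diagnosis (section 3), taken here as a median *m*; 12 participants, 4 per arm; final visit at Week 12.

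**Assumptions.** Exponential survival. The interval *d* from diagnosis to randomisation is not stated; 2 to 6 months is used.

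**1. Absolute survival with no treatment effect**

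With constant hazard, survival after entry has median *m*, so the median counted from diagnosis among entrants is *m* + *d*.

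- *m* = 12, *d* = 3: median 15 months instead of 12 (+25%).
- 12-month survival: 2^(−(12−3)/12) = 59.5%, instead of 50%.

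The mean is *m*/ln 2. With follow-up to death, the apparent death-rate ratio against an unselected from-diagnosis population is (*m*/ln 2) / (*m*/ln 2 + *d*):

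| *m* (months) | *m*/ln 2 | *d* = 2 | *d* = 3 | *d* = 6 |
|---|---|---|---|---|
| 9 | 12.98 | 0.87 | 0.81 | 0.68 |
| 12 | 17.31 | 0.90 | 0.85 | 0.74 |
| 14 | 20.20 | 0.91 | 0.87 | 0.77 |

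A value of 1.00 would be correct for an inert agent.

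**2. Between randomised arms**

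Simulated Cox hazard ratios: 100,000 patients, control median 12 months after randomisation, exponential lags.

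| Mean lag (months) | True HR | From randomisation | From diagnosis, no delayed entry | From diagnosis, delayed entry |
|---|---|---|---|---|
| 2 | 1.0 | 1.001 | 1.000 | 1.001 |
| 3 | 1.0 | 1.010 | 1.011 | 1.010 |
| 6 | 1.0 | 0.995 | 0.991 | 0.996 |
| 2 | 0.6 | 0.602 | 0.605 | 0.602 |
| 3 | 0.6 | 0.600 | 0.606 | 0.600 |
| 6 | 0.6 | 0.602 | 0.620 | 0.602 |

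The null is preserved and a real effect is slightly attenuated.

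Chance imbalance in the mean lag, 4 v 4, has standard deviation SD × √(2/4). For lag SDs of 2, 3 and 6 months this is 1.4, 2.1 and 4.2 months.

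**3. Cut-off, in weeks after the last randomisation**

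- Section 9.6, triggered by the 12th enrolment: week 12. Section 13.2: 12 + 12 = week 24. Gap 12 weeks.
- If enrolment means TILT consent 2 weeks after randomisation: 24 − 14 = 10 weeks.
- If recruitment closes on the calendar date *g* weeks after the last enrolment: 24 − (12 + *g*) = 12 − *g*. That is 8 weeks for *g* = 4 and zero for *g* = 12; beyond that the order reverses.

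Expected deaths with 12 entrants evenly spaced, median 12 months: 4.59 at the earlier date against about 5.7 at the later one for 12-month recruitment, and 5.59 against 6.53 for 18 months. Across medians of 9 to 14 months the later date adds about one death, or 15 to 25%.

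**The case against.** **A false benefit between arms.** A reader might infer that guaranteed survival time is credited to OK432 or BCG over control. The documents do not support that. Section 13.3 summarises outcomes by randomised arm, all arms carry the same expected lag, and the simulation shows no spurious effect.

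**Chance imbalance.** This is real but small. With 4.59 deaths there are about 1.53 per arm. The standard error of an arm median is then 12/√1.53 = 9.7 months, and of a difference 9.7 × √2 = 13.7. A lag SD of 4 months contributes 4 × √(2/4) = 2.8, and √(13.7² + 2.8²) = 14.0, about 2% more. The planned covariate and the 8-week subgroups ease it further.

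**Size against national data.** It is tempting to say that an inert agent is certain to beat national survival, or that the bias exceeds the 2.8-month chemotherapy gain quoted in the abstract. Both depend on the unstated lag. The subgroup under 8 weeks shows that early entrants are expected, and for them the inflation would be under 2 months. Eligibility also differs from a national population (catheter or suitable effusion, performance status, predicted survival of at least 12 weeks), which could shift survival either way. This limits the figure but does not remove the inflation.

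**Left to the SAP.** Survival set-up often is, and silence on delayed entry alone would be no finding. Here the protocol itself fixes the origin at diagnosis, the estimators and the external comparison.

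**Importance.** The primary outcome is feasibility and none of its three thresholds uses OS. Section 2.3 also plans further OS analyses 1 and 2 years after completion, so follow-up is not lost. This stands and lowers the severity.

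**Conclusion.** Two faults hold as written.

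First, OS from diagnosis without delayed entry inflates absolute survival and the planned comparison with national and earlier-trial data. The median rises by roughly the lag: 12 to 15 months for an assumed 3-month lag. The apparent death-rate ratio for an inert agent is 0.68 to 0.91. These figures assume exponential survival, the protocol's 9 to 14 months taken as a median, and lags of 2 to 6 months that the protocol does not give. The fault does not extend to the randomised comparison, where the effect is slight attenuation and a little added noise.

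Second, the cut-off for OS and the EoT date are defined incompatibly. The dates are 12 weeks apart if the 12th enrolment is the trigger and is counted from randomisation, and usually less if the calendar close applies. An unqualified 12-week gap would overstate it.

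Because OS is exploratory in a feasibility trial but informs the next trial's design, this should be fixed; it is not critical.

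**What to change.** - **Sections 2.3 and 13.2:** define OS from randomisation (Week 0) for all comparisons between arms, including the 1-year and 2-year analyses.
- **Section 13.3:** keep time from diagnosis to randomisation as a baseline covariate and drop the time-dependent label. For any comparison with national or historical survival from diagnosis, keep diagnosis as origin with delayed entry at randomisation.
- **Sections 2.3, 9.6 and 13.2:** state one OS cut-off, counted from the last randomised participant. Enrolment is a poor anchor: section 5.5 counts as TILT participants only those who sign TILT consent, controls never do, and only 8 of the 12 are to be offered it. Read literally, the 12th enrolment would never occur.

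The cost is a wording amendment and the origin and entry settings in the survival analysis. It uses the dates of diagnosis, randomisation and death that the planned analyses already require. The reported medians will be shorter and the external comparison less favourable.
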